3. To assess the extent to which the effects of *Parent Positive* on the primary conduct outcome are moderated by levels of (i) pre-existing levels of conduct problems and (ii) *Parent Positive* usage levels as monitored during the one month intervention period. Usage of *Parent Positive* will be monitored for two months for descriptive purposes.
4. To test the cost-effectiveness of *Parent Positive* compared to FAU over a two month follow-up period.
5. **Exploratory:** To assess whether the effects of *Parent Positive* on primary and secondary outcomes are moderated by baseline characteristics - family social economic status and composition, parental psychological distress, child age, symptoms of attention-deficit/hyperactivity disorder and emotional problems.
6. **Exploratory:** (ii) to explore the impact of lockdown circumstances and policies at baseline on the effects of *Parent Positive* on primary and secondary outcomes. Data on lockdown circumstances will be collected at one and two months post-randomisation for descriptive purposes.

Note that these exploratory aims may not be addressed in the primary trial results paper.

Hypotheses:

1. At both one and two months post-randomisation, *Parent Positive* will reduce the average levels of parent-reported child conduct problems in a self-selected community sample, when compared to FAU.
2. *Parent Positive* will reduce the average levels of parent psychological distress, parental child-related stress and worries, family conflict and child emotional problems (secondary outcomes) in comparison to FAU.
3. The effects on the primary outcome will be greater where (i) children had higher baseline levels of conduct problems (i.e., more need for *Parent Positive*) and (ii) parents spent more time using the app.
4. *Parent Positive* will be cost-effective compared to FAU as a result of improved outcomes and cost savings.
5. **Trial design**

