**Figure 1. SPARKLE enrolment and group allocation procedure.**

1. **Sample**

A total of 616 will be recruited into the trial with 308 consenting parents randomised to each arm following SPARKLE baseline assessments. This sample size was powered to address our primary question whether comparing outcomes at one month post-randomisation, *Parent Positive* will reduce children’s conduct problems observed as compared to FAU. During the first UK lockdown (i.e., March to June 2020) there was around an approximate 0.2 standard deviation increase in SDQ conduct problems scores reported by Co-SPACE parents with children aged 4-10. For the current study, we took this as representing the smallest between group difference that was of clinical value to detect between *Parent Positive* and FAU scores post-randomisation (i.e., Cohen’s *d* of 0.2). We assumed a within trial drop-out rate of 30%, a correlation of 0.5 between one pre- and two post-randomisation measures (Machin, Campbell, Tan, & Tan, 2018), and using a one-tailed (Parent Positive > FAU) and an alpha of .05 that this number of participants provides 90% power to test the one-sided hypothesis that *Parent Positive* is superior to FAU.

1. **Recruitment**

Participants will be recruited into SPARKLE from the pool of Co-SPACE families of children aged 4-10. Recruitment into the Co-SPACE study is ongoing using advertisements on social media and through circulating information about the study to primary schools and relevant organisations, so SPARKLE may also recruit participants that are new to Co-SPACE.

1. **Allocation**

Participants will be enrolled into the study online via the Quatrics platform. Following consenting, simple randomisation will be carried out remotely within the Qualtrics programme using the Randomizer function, after which the parents in the *Parent Positive* group will be given access to the app as in section 7.4 above. Enrolled participants will be allocated to *Parent Positive* or FAU at the ratio of 1:1 by simple randomisation. Neither blocking nor stratification will be used.

1. **Blinding**

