Briefly, a mixed effects linear analysis of covariance (ANCOVA) model with repeated measures will be used with **the SDQ conduct problem** scores at one (primary outcome) and two months (secondary outcomes) post-randomisation as the dependent variables, and intervention group, time point, intervention group by time point interaction, baseline SDQ conduct problem score, gender and age of child as independent variables, with the interaction term used to extract the primary and secondary outcome effects at the two time points. Similar statistical models will be used to test for intervention effects on the other secondary outcome scale scores (average levels of parent psychological distress, parental child-related stress and worries, family conflict and child emotional problems) at one and two months post-randomisation. All analysis will follow the intention to treat (ITT) principle as far as possible (Sullivan et al., 2018; White et al., 2012).

**Aim iii) Are the effects of *Parent Positive* on the primary conduct problem outcome** **moderated by levels of (i) pre-existing levels of conduct problems (subgroup analysis) and (ii) *Parent Positive* usage levels as monitored during the one month intervention period (post-randomisation intervention** **effect modification analysis).**

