As for the concept of adherence, the concept of per protocol analysis seems less sensible in this trial where the intervention is taking more of a public health approach with no specific direction of how and when to use, in a sample not restricted to those with a specific clinical need. In this sense, and for this particular intervention, there is not a “intervention protocol” that parents need to adhere to. However, an analysis of the extent to which effects depend on (i) pre-existing levels of child conduct problems and (ii) intervention uptake will help to interpret the value of the app. To address (i) in the mixed model for conduct problems described under Aims i and ii, the intervention by time interaction term will be replaced with an intervention by time by baseline conduct problems interaction. Intervention effects for different conduct problem scores will be extracted at the two time points. To address (ii) the effect of the app usage measure, total time accessing the Boosters zone during the one month intervening period, will be assessed using appropriate causal methods for post-randomisation variables measured only in the Parent Positive group (Dunn et al., 2015). Child gender and age will be entered as independent variables, as well as other variables that could be predictors of app usage (i.e., pre-existing levels of conduct problems). Usage of *Parent Positive* will be monitored for two months for descriptive purposes.

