**Aim v and vi) Exploratory – note these analyses may not be included in the primary trial results paper.**

**(v) Are the effects of *Parent Positive* on primary and secondary outcomes moderated by other baseline characteristics - parental psychological distress and child age, gender, ADHD symptoms and emotional problems**?

**(vi) Are the effects of *Parent Positive* on primary and secondary outcomes moderated by baseline lockdown-related circumstances – full vs. partial or no lockdown, whether parents are working from home or not, and whether children are being homeschooled or not.**

Similar models to those described for Aim iii will be used to explore whether i) these additional baseline characteristic variables and ii) lockdown-related circumstances moderate intervention effects on the outcomes. Child gender and age will be retained as independent variables in all models for consistency.

1. **Data Monitoring**

Given the short-term nature of the trial and rapid recruitment schedule, there is little opportunity to monitor data during the trial. As noted, the trial will have an independent TSC, but no DMC. The TSC will include an independent statistician and will be consulted as to whether they want any data reporting to be done during the trial. This will be included in the TSC Terms of Reference that will be agreed upon by the Committee. Given the duration of the trial and the nature of the intervention, there are no interim analysis or stopping rules either for efficacy or safety.

1. **Harms**

There are no known risks or harms associated with completing the intervention. However, parents will be informed through the information sheet that there is some possibility that using *Parent Positive* may result in them having new concerns about their child’s behaviour, their relationship with their child or their ability to manage as a parent. They will also be informed that this is the reason why we will ask them to report any physical or psychological difficulties during the study (see Adverse events). They will also be advised to contact their General Practitioner if they feel they need further support.

*Definitions*

Adverse event (AE): Any untoward medical occurrence in a clinical trial participant administered a research product or procedure which does not necessarily have a causal relationship with this treatment. Medical adverse events will be recorded using standard medical definitions.

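### Aim iii(i): taken literally, replacing the intervention-by-time term with the three-way term forces the effect at baseline score 0 to be equal at one and two months, which can distort the moderation estimates

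*Protocol*

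**What the plan says.** All references are to the Statistical analysis section of the protocol unless stated.

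- **Aims i and ii.** The model for SDQ conduct problems is listed term by term: "intervention group, time point, intervention group by time point interaction, baseline SDQ conduct problem score, gender and age of child as independent variables". The description is a summary, opening with "Briefly, a mixed effects linear analysis of covariance (ANCOVA) model with repeated measures will be used".
- **Aim iii(i).** The same model is changed in one respect: "the intervention by time interaction term will be replaced with an intervention by time by baseline conduct problems interaction". The text does not say whether intervention-by-baseline and time-by-baseline terms come in with it.
- **Output for Aim iii(i).** The next sentence is "Intervention effects for different conduct problem scores will be extracted at the two time points".
- **Aims v and vi.** "Similar models to those described for Aim iii will be used to explore" whether further baseline characteristics and lockdown circumstances moderate the effects.
- **Objectives, hypothesis 3(i).** The effect on the primary outcome is expected to be greater where "children had higher baseline levels of conduct problems".

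**The concern.** The Aim iii(i) sentence states an operation on a listed model: one term out, one term in. Carried out exactly, it leaves intervention, time, baseline score, gender, age and a three-way term. That model is not hierarchical.

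The main model uses intervention-by-time to let the effect differ between one month (primary) and two months (secondary). Dropping it takes away part of that freedom in the very analysis that is meant to report effects at each time point.

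At stake is a named, non-exploratory aim with a directional hypothesis. A change in the effect over time could appear as moderation by baseline severity, or could hide it. Because Aims v and vi reuse the structure, the same problem carries to any continuous moderator there.

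**Working it through.** **The plan's own figure.** The protocol gives no figure for the moderation analysis. Its sample size reproduces, using d = 0.2, correlation 0.5, one pre and two post measures, one-sided 0.05, 90% power and 30% drop-out. The variance factor is (1 + 0.5)/2 - 0.5² = 0.5. This gives 215 per arm, 215/0.7 rounded up is 308, and the total is 616. Nothing below changes it.

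**Notation.** G = arm, T = time point, X = baseline score. Let the true effect be a₂ + b₂X at one month and a₃ + b₃X at two months, and let δ = a₃ - a₂. Gender and age do not alter the argument.

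**Step 1, factor coding (the most favourable literal reading).** The terms G, T, X and G×T×X with G and T as factors give a separate X slope in each of the four arm-by-time cells, but only additive intercepts. The design has rank 7; the full factorial has rank 8. The missing dimension is G×T, so the fitted effect at X = 0 must be equal at both times.

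**Step 2, size of the bias.** Assume 1:1 allocation, complete follow-up, and baseline mean m and SD s. The two-month minus one-month difference then has a common intercept for both arms where the truth needs intercepts δ apart. Each arm is off by δ/2, and its slope absorbs what it can, (δ/2)·m/(m² + s²). Hence

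- bias in the one-month slope = -(δ/2)·m/(m² + s²);
- bias in the two-month slope = +(δ/2)·m/(m² + s²);
- fitted effect at score 0 = (a₂ + a₃)/2 at both times.

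A numerical check gave the same values for within-person correlations of 0, 0.5 and 0.8.

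**Step 3, numbers.** The protocol gives no mean or SD for the score. Assume m = 1.99 and s = 1.6. Then m/(m² + s²) = 1.99/(3.96 + 2.56) = 0.305. For a fade from -0.3 to -0.1, δ = 0.2:

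- one-month slope bias = -0.1 × 0.305 = -0.03, although true moderation is zero;
- one-month effect at score 0 = (-0.3 - 0.1)/2 = -0.20, against a true -0.30;
- one-month effect at score 5 = -0.20 - 5 × 0.0305 = -0.35, against a true -0.30.

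The spurious gap between scores 0 and 5 is 0.15 points. The target effect ("i.e., Cohen’s *d* of 0.2") would be 0.2 × 1.6 = 0.32 points on the same assumption, so the gap is about half of it. With m = 2 and s from 1.2 to 2.0, the slope bias runs from -0.1 × 2/5.44 = -0.037 to -0.1 × 2/8 = -0.025.

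**Step 4, simulation** (500,000 participants, least squares, same assumed distribution). Fitted one-month slopes:

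| True effect at score 0 (1 / 2 months) | True slope (1 / 2 months) | Literal, factor | Product, T = 0/1 | Product, T = 1/2 | Full hierarchical |
|---|---|---|---|---|---|
| 0 / 0 | -0.10 / -0.10 | -0.097 | 0.000 | -0.055 | -0.096 |
| 0 / -0.2 | -0.10 / -0.10 | -0.070 | 0.000 | -0.068 | -0.101 |
| 0 / 0 | -0.15 / -0.05 | -0.152 | 0.000 | -0.028 | -0.150 |
| -0.3 / -0.3 | 0 / 0 | 0.000 | 0.000 | -0.008 | 0.000 |
| -0.3 / -0.1 | 0 / 0 | -0.029 | 0.000 | 0.005 | 0.002 |

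**Step 5, numeric product.** If the three-way term is one column G·T·X, the constraint is algebraic. With T = 0 at one month the column is zero there, so one-month moderation is 0 whatever the data show. With T = 1 and 2, the one-month slope is exactly half the two-month slope.

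**Step 6, two-level moderators.** With factor coding, the main effects plus the three-way term span all eight cells (rank 8, as for the full factorial). Gender in Aim v and the lockdown contrasts of Aim vi are then unconstrained.

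**The case against.** The strongest reply is that naming only the highest-order interaction is common shorthand for a model that contains its lower-order terms. The protocol never says those terms are left out, the description is expressly brief, and a statistical analysis plan may list them. The extraction sentence also shows that a sensible model was intended.

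Much of this stands. The intent is clear, and the sentence may be loose wording only. But in a hierarchical model nothing is replaced, because intervention-by-time stays. The Aims i and ii text also writes out its lower-order terms, so a reader who follows the protocol's own style would drop the term. This is a stated rule that gives a wrong result if followed, not a detail left for later.

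Three stronger readings are tempting, and the documents do not support them.

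- **A reader might infer that one-month moderation cannot be estimated, or is zero by construction.** That needs a hand-coded numeric product with 0/1 time. The extraction sentence argues against it, since every score would have the same one-month effect. Under factor coding the one-month slope is estimable, and it is unbiased when the effect at score 0 is constant over time.
- **A reader might infer that the three-way coefficient is the test of Aim iii(i).** The protocol does not say so; it names score-specific effects at each time point.
- **A reader might infer that every Aim v and vi analysis is biased.** Two-level moderators are not, under factor coding. Those aims are also exploratory and promise only similar models.

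**Conclusion.** The point holds as a specification error of moderate weight. Followed literally with factor coding, the Aim iii(i) model forces an equal intervention effect at score 0 at one and two months. The one-month slope is then off by -(δ/2)·m/(m² + s²), which is about 0.03 points per baseline point for a 0.2-point change over time. The sign depends on the direction of change: a fading effect produces an artefact in the direction of hypothesis 3(i), and a growing effect masks true moderation. If the effect at score 0 does not change, there is no bias.

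The constraints, including the coding dependence of a numeric product, follow from the model and need no assumed data. The magnitudes rest on an assumed baseline mean near 2 and SD near 1.6, illustrative effects, complete follow-up, and the baseline score entered uncentred, since the protocol mentions no centring. If it were centred at its mean, m = 0 and the slope bias vanishes, but the effect at the mean would be forced equal at both times instead.

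Aim iii(i) and the continuous moderators of Aim v (parental distress, child age, ADHD symptoms, emotional problems) are affected. The primary analysis and the sample size of 616 are not.

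**What to change.** Reword the Aim iii(i) sentence so that the three-way term is added, not substituted. For example: the intervention-by-time-by-baseline interaction will be added to the model together with all its lower-order terms (intervention-by-time, intervention-by-baseline, time-by-baseline and the main effects), with intervention and time as factors; Aim iii(i) will be tested by the intervention-by-baseline contrast at one month, and score-specific effects at both time points will be taken from the same model.

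State that Aims v and vi use the same structure, including the moderator's main effect where it is not already in the model.

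The cost is one or two sentences and no new data. Relative to the main model, it adds three parameters for Aim iii(i), and four for a continuous or two-level moderator not already in the model. After the planned 30% drop-out about 431 families remain (616 × 0.7), so the loss of degrees of freedom is negligible.

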**Aim iv) Is *Parent Positive* cost-effective compared to FAU over a two month follow-up period.**

The primary economic evaluation will be a cost-utility analysis carried out two months post-randomisation and taking the National Health Service (NHS) and personal social services perspective preferred by National Institute for Health and Care Excellence (NICE), including any education-based health and social services, given the age of the population. Using data from the CA-SUS, all services will be costed using nationally applicable unit costs (e.g., Personal Social Services Research Unit Costs of Health and Social Care, NHS Reference Costs, British National Formulary for medications). The *Parent Positive* costs will be estimated in consultation with intervention developers.

At both time points (one and two months post-randomisation), utility weights for children will be derived from the SDQ using a published mapping algorithm (Furber, Segal, Leach, & Cocks, 2014) that transforms SDQ subscale scores into Child Health Utility 9 Dimensions (CHU-9D; Stevens, 2010) scores which can then be used to estimate quality adjusted life years (QALYs) between baseline and two month follow-up.

Costs and outcomes will be compared in terms of mean differences and 95% confidence intervals from non-parametric bootstrap regressions (1,000 replications) to account for non-normal distribution common to economic data. Cost-effectiveness will be assessed using the net benefit approach following standard approaches (Drummond, Sculpher, Claxton, Stoddart, & Torrance, 2015). A joint distribution of incremental mean costs and effects for the two groups will be generated using non-parametric bootstrapping to explore the probability that each of the intervention conditions is the optimal choice, subject to a range of possible maximum values (ceiling ratio) that a decision-maker might be willing to pay for improvements in outcome (QALYs). Cost-effectiveness will be explored using incremental cost effectiveness ratios (Briggs, 1999) with uncertainty represented by cost-effectiveness planes and cost-effectiveness acceptability curves (Fenwick, Claxton, & Sculpher, 2001).

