  4. **Permitted concomitant care.** There will be no restrictions on concomitant care which will be monitored through collection of information on service use and harms.

1. **Measures and Outcomes**

[Co-SPACE](http://cospaceoxford.org/) routinely collects a wide range of measures. In this protocol we only describe those measures that will be included in the SPARKLE analysis. See Table 1 for the schedule of data collection for each measure. Where there are specific instructions for dealing with missing data for each measure, these will be followed. Where there are no specific instructions for missing data, we will prorate at the subscale level where there are 20% or fewer missing subscale items. For measures with no subscales, we will prorate at the overall scale level where there are 20% or fewer missing items overall.

- 1. **Child outcomes**
     1. **Conduct problems (T1 co-variate; primary outcome T2; secondary outcome T3; T1 moderator)**: This will be measured using the parent-rated conduct problems subscale of the Strengths and Difficulties Questionnaire (SDQ; Goodman, 1997). This is a widely used and validated five item subscale measuring oppositional, defiant and disruptive behaviour rated on a 3-point Likert scale (not true, somewhat true, and certainly true), with a mix of positive and negatively phrased items. Individual items’ scores are summed to derive an overall symptom subscale score. The level of ‘caseness’ at baseline will be presented for descriptive purposes. Data from this measure have been routinely collected from the Co-SPACE cohort every month.

Child conduct problems score was selected as the primary outcome because of the Co-SPACE finding reported above of a significant increase in average levels in the community since early on in the UK pandemic.

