     1. **Parental child-related stress and worries levels (T1 co-variate; T2 and T3 secondary outcomes):** This is based on five items routinely measured in Co-SPACE regarding children’s behaviour, wellbeing, screen time use, education and future using a 4-point Likert scale (not at all, a little, quite a lot, a great deal). Individual questions’ scores are summed to generate a single score. The scale has an adequate level of internal consistency (Cronbach alpha > .70) and re-test reliability (*r* = .71) amongst Co-SPACE parents.
     2. **Family conflict (T1 co-variate; T2 and T3 secondary outcomes):** This is based on three items routinely collected in Co-SPACE relating to arguments between parents, parents and children and siblings which are measured on a 4-point Likert scale (not at all, a bit, a lot, completely). The three questions are summed to generate a total score. The scale has acceptable internal consistency (Cronbach alpha > .54) and test-retest reliability (*r* = .73) amongst Co-SPACE parents.
     3. **Parental psychological distress (T1 co-variate; T2 and T3 secondary outcome; T1 moderator):** The Depression, Anxiety and Stress Scales-21 (DASS-21) is a widely validated 21-item self-report questionnaire measuring adult depression, anxiety and stress (Lovibond & Lovibond, 1995). Each of these three subscales consists of seven items rated on a 4-point Likert scale (did not apply to me at all; applied to me to some degree, or some of the time; applied to me to a considerable degree, or a good part of the time, applied to me very much, or most of the time), which are summed to obtain a single subscale score. The subscales scores will be summed and multiplied by two to form a single psychological distress measure comparable to the DASS-42 measure.
  2. **Other measures**
     1. **ADHD symptoms (T1 moderator; T1, T2 and T3 for QALYs calculation)**: measured with the inattention/overactivity subscale of the SDQ (Goodman, 1997). This five-item subscale measures restlessness, overactivity and inattention rated on 3-point Likert scales (not true, somewhat true, and certainly true), with a mix of positive and negatively phrased items. Individual items’ scores are summed to derive an overall symptoms subscale score.

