     2. **Peer problems (T1, T2 and T3 for QALYs calculation)**: measured with the peer problems subscale of the SDQ (Goodman, 1997). This five-item subscale measures difficulties in peer relationships and bullying rated on 3-point Likert scales (not true, somewhat true, and certainly true), with a mix of positive and negatively phrased items. Individual items’ scores are summed to derive an overall peer problems subscale score.
     3. **Prosocial behaviour (T1, T2 and T3 for QALYs calculation)**: measured with the prosocial behaviour subscale of the SDQ (Goodman, 1997). This five-item subscale measures difficulties in peer relationships and bullying rated on 3-point Likert scales (not true, somewhat true, and certainly true), with positively phrased items. Individual items’ scores are summed to derive an overall prosocial subscale score with higher scores indicating more prosocial behaviour.
     4. **Attitudes to Parent Positive (T2 and T3, intervention arm only):** Parent mean ratings of *Parent Positive* using a questionnaire, consisting of three items measuring parents’ ratings of the usefulness of each individual zone rated on a 7-point scale (1 = not useful at all to 7 = very useful), which will be summed up to derive an overall app usefulness score. The questionnaire will also capture parents’ descriptive and qualitative views of *Parent Positive* – both positive and negative.
     5. **Estimate of resource use for the health economic analysis (T2 and T3):** Information about the child’s use over the two-month follow-up period of key health and social services (high cost, high volume) known from published studies to be of relevance to the current population will be collected using a modified version of the Child and Adolescent Service Use Schedule (CA-SUS; Barrett et al., 2012). The CA-SUS will be completed by the parent at T2 and T3, covering the previous month. This measure has been developed and successfully applied in a range of populations of young people with mental health conditions, including self-complete versions, and will be based primarily on an online, self-completed parent-reported version of the CA-SUS designed for use in a current, related study (the NIHR funded OPTIMA trial - On-Line Parent Training for the Initial Management of ADHD referrals; RP-PG-0618-20003).

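### The Aim iv text leaves baseline out of the utility time points although its QALYs start at baseline, and it names no baseline-utility covariate for the QALY regressions

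*Protocol*

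**What the plan says.** Statistical analysis, Aim iv, makes a cost-utility analysis at two months the primary economic evaluation. On utilities it states: "At both time points (one and two months post-randomisation), utility weights for children will be derived from the SDQ". The mapped values are then used to "estimate quality adjusted life years (QALYs) between baseline and two month follow-up".

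Measures and Outcomes, Other measures, gives a different list of time points. The ADHD subscale is labelled "T1 moderator; T1, T2 and T3 for QALYs calculation", and the peer problems and prosocial subscales also carry the label "T1, T2 and T3 for QALYs calculation". The conduct subscale has a T1 role as well ("T1 co-variate; primary outcome T2; secondary outcome T3; T1 moderator"), and Table 1 schedules all five SDQ subscales at baseline and at both follow-ups.

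On the comparison between arms, Aim iv says: "Costs and outcomes will be compared in terms of mean differences and 95% confidence intervals from non-parametric bootstrap regressions". It lists no covariates. The clinical model under Aims i and ii, by contrast, names the baseline score and the child's gender and age. The Allocation section specifies simple 1:1 randomisation without blocks or strata.

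**The concern.** A QALY that accumulates from baseline needs a utility at baseline. The Aim iv sentence closes its list at two follow-up points, so an analyst working from that section alone would have to invent a rule for the first month. The choice changes the estimated QALY difference, and with it the cost-effectiveness ratio.

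The covariates are a second, weaker point. Once the baseline utility enters the QALY, it makes up part of every participant's outcome and is also correlated with the rest of it. Nothing in the randomisation limits chance imbalance on it. If the regression has no baseline-utility term, that variation stays in the estimated difference and widens its interval, although the data that would remove it are already collected.

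**Working it through.** **1. The passages side by side.**

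| Place | Time points for utility or QALY |
|---|---|
| Aim iv, derivation of utilities | one and two months |
| Aim iv, QALY period | baseline to two months |
| Other measures: ADHD, peer, prosocial | T1, T2, T3 |
| Table 1: all five SDQ subscales | collected at T1, T2, T3 |

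The first row conflicts with the other three.

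**2. Does the reading matter?** Let u1, u2 and u3 be utility at T1, T2 and T3. The trapezoidal rule is assumed, because the protocol does not name one.

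- Three-point QALY = (u1 + 2·u2 + u3)/24 years. As a share of the two-month period the weights are 0.25, 0.50 and 0.25.
- Suppose an effect of 0.2 SD at each follow-up (the Sample section's d, carried over to utilities). The difference is (0.50 + 0.25) × 0.2 = 0.15 SD.
- With utilities at two points only, one possible rule carries the one-month value back to baseline. The weights become 0.75 and 0.25, and the difference is (0.75 + 0.25) × 0.2 = 0.20 SD, one third larger.

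**3. The plan's own figure.** The protocol gives no precision for QALYs. Its sample size rests on a correlation of 0.5, with one measure before and two after randomisation.

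- Variance factor: (1 + 0.5)/2 − 0.5² = 0.50.
- n per arm = 2 × (1.645 + 1.282)² × 0.50/0.2², which rounds up to 215.
- With 30% drop-out: 215/0.70, rounded up to 308 per arm, or 616 in total.

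This agrees with the Sample section. It concerns the conduct score and does not depend on the present point.

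**4. Value of adjusting for baseline utility.** Assume equal variances (set to 1) and the same correlation ρ between any two time points.

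- Variance of the QALY: V = 0.375 + 0.625ρ
- Covariance with u1: C = 0.25 + 0.75ρ
- Variance after adjustment: V − C²

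| ρ | V | C | V − C² | Ratio to V | Variance cut |
|---|---|---|---|---|---|
| 0.3 | 0.5625 | 0.475 | 0.3369 | 0.599 | 40% |
| 0.5 | 0.6875 | 0.625 | 0.2969 | 0.432 | 57% |
| 0.7 | 0.8125 | 0.775 | 0.2119 | 0.261 | 74% |

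At ρ = 0.5 the adjusted interval is √0.432 = 0.657 times as wide, so 34% narrower. Put the other way, the unadjusted standard error is 1.52 times as large.

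**5. Size of a chance imbalance.** Completers per arm: 308 × 0.70 ≈ 216. The standard error of the baseline difference is √(2/216) = 0.096 SD. At ρ = 0.5, an imbalance of one standard error shifts the unadjusted QALY difference by 0.625 × 0.096 = 0.060 SD on average, or 0.060/0.15 = 40% of the illustrative effect (31% at ρ = 0.3, 50% at ρ = 0.7). Cancelling that effect through baseline imbalance alone would take about 0.15/0.060 = 2.5 standard errors.

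**The case against.** The best defence is that the baseline utility is not missing. The measures section expressly earmarks T1 data for the QALYs, all five subscales are collected at T1, and Aim iv itself starts the QALY period at baseline. A reader might infer from the Aim iv sentence that utilities will exist only at the follow-ups. The rest of the protocol does not support that. This part of the defence stands: it reduces the point to an inconsistency. It does not remove the point, because the sentence that fixes the derivation still gives the wrong list.

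A reader might also infer that the sponsor has decided against baseline adjustment. The documents do not say so. Aim iv plans regressions and lists no covariates, so it neither includes nor excludes baseline utility, and such a list is commonly left to a statistical or health economic analysis plan that is not at hand. The contrast with the clinical model shows a difference in detail, not a decision. The second half of the point is therefore a request to state the covariate, not a charge that the analysis is wrong.

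Finally, a reader might conclude that baseline noise would dominate the sign of the QALY difference, or bias it. Neither is shown. Under randomisation the unadjusted difference is unbiased, and its bootstrap interval already reflects chance imbalance. With the illustrative effect, reversal through imbalance alone would need about 2.5 standard errors. A smaller utility effect would lower that figure, but the protocol gives no utility effect from which to work.

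**Conclusion.** The contradiction holds and can be checked on the page: the Aim iv text names two utility time points where its own QALY period and the measures section require three. It affects a rule that enters the primary economic result; one possible two-point rule would raise the illustrative difference from 0.15 to 0.20 SD.

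On adjustment, the protocol is silent, and naming baseline utility is a gain at no cost in data. The gain of about 57% in variance (40% to 74% for correlations of 0.3 to 0.7) is an illustration. It rests on a trapezoidal QALY, equal variances, a common correlation across time points, and a value of 0.5 taken from the conduct-score sample size; the protocol gives none of these for mapped utilities. The issue is one of precision, not bias. It is confined to Aim iv and leaves the primary conduct analysis and the total of 616 untouched.

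**What to change.** In Statistical analysis, Aim iv:

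1. Replace the two follow-up points with all three, so that utilities are derived from the SDQ at baseline (T1), one month (T2) and two months (T3), in line with the measures section.
2. Add to the sentence on bootstrap regressions that the QALY and net-benefit models include baseline utility as a covariate, or confirm this in the health economic analysis plan.

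The cost is two phrases. The T1 SDQ is already scheduled for every participant, so no data collection, sample size or primary analysis changes.
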